#### 6.4.2 Imputation method

In case, a given variable has more than 10% missing data, multiple imputation will be applied. All the existing data of that variable will be used to predict the missing values.

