## 8.0 STATISTICAL CONSIDERATIONS

### 8.1 SAMPLE SIZE

We will compare the quadriceps muscle strength between two groups of ACL reconstructed individuals: 1) with and 2) without knee pain.

The variance in this population is unknown, while our sample size estimation will be pragmatic. To detect a group difference of 0.3 Nm/kg in the primary outcome with a common standard deviation of 0.5 Nm/kg, a sample size of 120 with a 1:3 group allocation ( $n=30$  symptomatic;  $n=90$  asymptomatic) will be required.

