### 3.2 SAMPLE SIZE, POWER AND DETECTABLE DIFFERENCE

We will compare the quadriceps muscle strength between two groups of ACL reconstructed individuals: 1) symptomatic and 2) asymptomatic.

The variance in this population is unknown, while our sample size estimation will be pragmatic. To detect a group difference of 0.3 Nm/kg in the primary outcome with a common standard deviation of 0.5 Nm/kg, a sample size of 50 per group will have a power of 84%, ( $\alpha = 0.05$ ). Thus, a total sample size of  $n=100$  (50/50 per group) was originally intended to be applied. However, in November 2021 71 (17/54 symptomatic/asymptomatic) participants were recruited and included in the study, indicating a low prevalence of symptomatic participants. We estimated that it would be difficult to recruit

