## STATISTICAL ANALYSIS PLAN: MIRAKOS

50 symptomatic participants within the time allotted for recruitment (scheduled to last until August 2022). In contrast, the recruitment of participants to the asymptomatic group has proven to be efficient. Therefore, we decided to re-calculate the sample size and change the group allocation ratio from 1:1 to 1:3. To detect that same group difference with the same common standard deviation of the primary outcome as stated above, a new total sample size was estimated to  $n=120$  ( $n=30$  symptomatic and  $n=90$  asymptomatic participants) with a statistical power of 80.6%. This amendment was registered in the study protocol 4th November 2021. Currently, our goal is to continue the data collection until the inclusion of 120 eligible participants (symptomatic/asymptomatic;  $n=30/90$ ) is reached. However, the inclusion of participants will end in August 2022, leaving some uncertainty about the final sample size.

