### 6.4 MISSING DATA

#### 6.4.1 Reasons for missing data

Missing data may potentially occur due to technical issues, electrical power supply breakdown, or other unforeseen issues related to the test equipment. If this should happen the missing data will be considered as missing completely at random.

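### Followed as written, the SAP's multiple imputation rule leaves out study group and shrinks the between-group difference by about the fraction missing

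*Combined protocol and SAP*

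**What the plan says.** SAP 6.4.2 is the whole imputation rule. The trigger is "In case, a given variable has more than 10% missing data, multiple imputation will be applied", and the predictors are given as "All the existing data of that variable will be used to predict the missing values". It names no group term, other outcome, auxiliary variable, model type or number of imputations.

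SAP 6.4.1 lists technical, power-supply and equipment problems as possible causes and says that in that event "the missing data will be considered as missing completely at random".

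Nothing elsewhere fills the gap. SAP 5.6 rules out covariate adjustment, so group cannot be inferred from a covariate list. The rules for KOOS, IKDC and ICOAP in 6.2.3 to 6.2.5 deal with single missing items inside a questionnaire. SAP 6.3.1 makes the between-group mean difference, with its 95% confidence interval, the result reported for continuous outcomes.

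**The concern.** An imputation model should contain the variables of the analysis that follows. Here that analysis compares two groups. If group is absent from the imputation model, a missing symptomatic value and a missing asymptomatic value are drawn from the same pooled distribution. The completed data then contain a share of values with no group difference, and the estimate is diluted by that share.

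This happens even when data are MCAR. Under that assumption an analysis of the observed cases is unbiased, so the rule would introduce a bias that was not there before. It covers every variable, including the primary outcome and the six key secondary outcomes, and it takes effect only when missing data are material. The planned power leaves little room for such a loss.

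**Working it through.** **Inputs from the documents**
- Difference and SD: "To detect a group difference of 0.3 Nm/kg in the primary outcome with a common standard deviation of 0.5 Nm/kg" (SAP 3.2).
- Size: "a sample size of 120 with a 1:3 group allocation" (protocol 8.1), that is 30 symptomatic and 90 asymptomatic. SAP 3.2 records the decision to "change the group allocation ratio from 1:1 to 1:3".
- Significance level 0.05 (SAP 6.3.1). Sidedness is not stated; two-sided is assumed because it reproduces the stated power.
- No covariates (SAP 5.6), so the contrast is an unadjusted mean difference.

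**Assumed, because the documents give no figure**
- Missing fraction m = 15%, 20% and 30%, or 18, 24 and 36 of 120. Exactly 10% (12 of 120) does not trigger the rule; 13 of 120 does.

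**Step 1. The plan's own power**
- 30/90: SE = 0.5 × √(1/30 + 1/90) = 0.1054, and 0.3/0.1054 = 2.85. The noncentral t with 118 df gives 80.6%. The SAP says "with a statistical power of 80.6"%, so the figure is reproduced.
- 50/50: SE = 0.5 × √(2/50) = 0.10, and 0.3/0.10 = 3.0. With 98 df this gives 84.4%. The SAP says "a sample size of 50 per group will have a power of 84"%, also reproduced.

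**Step 2. Expected difference without group in the model**
Let δ be the true difference, a and b the missing fractions in the symptomatic and asymptomatic groups, and w the symptomatic share of the observed values. Imputed values in both groups have the pooled observed mean as their expectation.
- The completed symptomatic mean moves towards the asymptomatic mean by a(1 − w)δ.
- The completed asymptomatic mean moves towards the symptomatic mean by bwδ.
- The expected difference is δ[1 − a(1 − w) − bw].

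With a = b = m this is (1 − m)δ:
- m = 15%: 0.85 × 0.30 = 0.255
- m = 20%: 0.80 × 0.30 = 0.240
- m = 30%: 0.70 × 0.30 = 0.210

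With unequal fractions the pull is a weighted mix of a and b, still towards zero.

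**Step 3. Simulation**
For each scenario, 2,000 datasets were generated with 30/90 participants, SD 0.5 and values missing completely at random. Imputation used a Bayesian normal model with 20 imputations, combined by Rubin's rules with small-sample degrees of freedom. The Monte Carlo standard error of a power figure is at most √(0.5 × 0.5/2000), about 1.1 percentage points.

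| True difference 0.30 Nm/kg | 15% missing | 20% missing | 30% missing |
|---|---|---|---|
| Mean estimate, observed cases | 0.299 | 0.299 | 0.300 |
| Mean estimate, imputed without group | 0.254 | 0.239 | 0.209 |
| Mean estimate, imputed with group | 0.299 | 0.299 | 0.301 |
| Power, observed cases | 73.5% | 71.3% | 65.6% |
| Power, imputed without group | 60.1% | 51.4% | 34.4% |
| Power, imputed with group | 72.3% | 69.9% | 64.2% |
| Mean SE, observed cases | 0.114 | 0.118 | 0.126 |
| Mean SE, imputed without group | 0.115 | 0.118 | 0.124 |
| RMSE, observed cases | 0.114 | 0.118 | 0.129 |
| RMSE, imputed without group | 0.108 | 0.114 | 0.129 |
| 95% CI coverage, observed cases | 95.3% | 94.9% | 94.2% |
| 95% CI coverage, imputed without group | 96.2% | 96.1% | 94.5% |

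The simulated means agree with Step 2. With no true difference, imputation without group rejects in 2.5%, 1.5% and 0.9% of datasets instead of the nominal 5%, so the test is over-conservative.

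**The case against.** **The SAP does not exclude group.** A reader might infer that the plan has chosen a model without group. The sentence does not say *only*, and it could mean that every observed record of the variable is used. If imputation within groups was intended, the bias disappears. This stands as a limit on the point. But the variable itself is the only predictor source named, and no other section supplies group, so a programmer following the text would leave it out.

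**The rule may never operate.** Most data come from one visit, SAP 5.4 expects negligible withdrawal, the primary outcome is the best of three contractions, and walking trials are repeated until enough are acceptable. This also stands: the documents do not support saying that the primary result will be biased, only that it would be if the trigger were passed.

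**Worse than no imputation?** That is tempting but too broad. It holds for bias and power. Because of the shrinkage, RMSE is slightly lower than with observed cases at 15% and 20% missing and equal at 30%, and coverage stays near 95%.

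**The error is conservative, in a study that SAP 4.1 calls exploratory.** True, and it lowers the stakes. But the study tests directional hypotheses and reports the size of the difference, which would be understated.

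**Pain-related missingness.** A reader might infer that SAP 6.4.1 declares all missing data MCAR. It does not; the statement is tied to equipment-related causes. Tests not completed because of pain simply have no rule. They are foreseeable, since one group is defined by knee pain and the tests are maximal contractions and fast lunges, but the documents give no indication of how often this would happen.

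**Conclusion.** The point holds for the rule as written. With equal missing fractions, the expected between-group difference is multiplied by (1 − m), under the SAP's own MCAR assumption and with no gain in precision that matters. For the planned 0.30 Nm/kg with 30/90 participants, the loss of power against observed cases is about 13, 20 and 31 percentage points at 15%, 20% and 30% missing (73.5 − 60.1, 71.3 − 51.4, 65.6 − 34.4).

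These sizes rest on three things: the literal reading of 6.4.2, missing fractions that are assumed here, and the 10% trigger being passed. The direction of the bias and the (1 − m) factor follow from algebra once group is absent from the model. Putting group in removes the bias. Because it adds little else under MCAR, power then stays close to that of observed cases.

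**What to change.** In SAP 6.4.2, state that the imputation model includes study group, or that imputation is done separately by group. Give the number of imputations, and report the observed-case analysis alongside.

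Optional additions:
- Use correlated outcomes and characteristics that are already collected (for example hamstring strength, knee extensor moments, pain ratings during tests, KOOS, sex, age, BMI, time since surgery) as auxiliary predictors. They would serve the imputation only; SAP 5.6 has no analysis covariates and need not change.
- In 6.4.1, record tests not completed because of pain as a separate reason for missing data, with a sensitivity analysis if there are any.

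The cost is a sentence or two of SAP text, logged as a revision, and a longer variable list or a by-group run in the SAS imputation step. No extra data are needed.

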### 6.5 STATISTICAL SOFTWARE

The analyses are done using the statistical software SAS version 9.4 (SAS Institute Inc., Cary, NC, USA).

## 7.0 DISCUSSION

The overall aim of the MIRAKOS study is to compare the musculoskeletal function between ACL reconstructed individuals with and without knee pain to answer the research question: Are there differences in the musculoskeletal function in ACL reconstructed individuals with knee pain when compared to those without knee pain? Specifically, we will test two hypotheses:

- 1) ACL reconstructed individuals without knee pain have stronger quadriceps muscles compared to those with knee pain.
- 2) ACL reconstructed individuals without knee pain develop higher quadriceps muscle forces and knee joint loading during walking and forward lunging compared to those with knee pain.

The rationale for the hypotheses is based on research documenting that quadriceps muscle weakness is associated with an increased risk of worsening symptoms and functional deterioration in people

## STATISTICAL ANALYSIS PLAN: MIRAKOS

with and at risk for radiographic knee OA, and that knee joint pain has a negative impact on quadriceps muscle activation and force production.

Although, the aim is to test these hypotheses we are fully aware of the fact that the cross-sectional study design will render our analyses exploratory. We will be able to describe and quantify possible differences in the musculoskeletal function between the two study groups; and then likely generate new hypotheses that may be investigated in future studies designed to determine causations.

### **8.0 CONCLUSION**

This SAP presents the basis for the analyses and outcome selection in the MIRAKOS cross-sectional study and discusses the methodological and statistical concerns associated with it. We aim to report the results of the MIRAKOS study as transparently and clearly as possible in order to mitigate outcome reporting bias and data-driven results.

## 9.0 TABLES AND FIGURES

**Figure 1.** Flow diagram (example)

[figure not shown]

# STATISTICAL ANALYSIS PLAN: MIRAKOS

**Table 1.** Overview of all measured variables.

| Variable                                               | At study visit | Not at study visit (tool)     |
|--------------------------------------------------------|----------------|-------------------------------|
| Demographic/Clinical                            |                |                               |
| Age                                                    | X              |                               |
| Sex                                                    | X              |                               |
| Height                                                 | X              |                               |
| Weight                                                 | X              |                               |
| Body mass index                                        | X              |                               |
| Injury situation                                       | X              |                               |
| Injured knee (side)                                    | X              |                               |
| Reconstruction graft type                              |                | X (DLR Register)              |
| Time since surgery (month)                             |                | X (DLR Register)              |
| Knee joint laxity                                      | X              |                               |
| Radiographic knee OA level (K-L score)                 | X              |                               |
| Questionnaires                                  |                |                               |
| Pre-injury activity level (Tegner score)               | X              |                               |
| Current activity level (Tegner score)                  | X              |                               |
| Knee function (IKDC)                                   | X              |                               |
| Knee function (KOOS)                                   | X              |                               |
| Knee pain experience (ICOAP)                           | X              |                               |
| Muscle strength                                 |                |                               |
| Maximal isometric quadriceps strength                  | X              |                               |
| Maximal isometric hamstring strength                   | X              |                               |
| Movement biomechanics                           |                |                               |
| Walking speed                                          | X              |                               |
| Peak knee extensor moment (walking/forward lunge)      |                | X (musculoskeletal modelling) |
| Peak knee flexion angle (walking/ forward lunge)       |                | X (musculoskeletal modelling) |
| Forward lunge movement time                            |                | X (musculoskeletal modelling) |
| Peak quadriceps muscle force (walking/ forward lunge)  |                | X (musculoskeletal modelling) |
| Peak knee joint contact force (walking/ forward lunge) |                | X (musculoskeletal modelling) |
| Knee pain                                       |                |                               |
| VRS during muscle strength tests                       | X              |                               |
| VRS during walking/forward lunge tests                 | X              |                               |
| Pressure pain sensitivity                       |                |                               |
| Pressure pain detection threshold (PDT)                | X              |                               |
| Pressure pain tolerance threshold (PTT)                | X              |                               |
|                                                        |                |                               |

# STATISTICAL ANALYSIS PLAN: MIRAKOS

**Table 2.** Participant characteristics

| Variable                                                                                                                                                                                                                                                                                                        | Asymptomatic
(N=xx) | Symptomatic
(N=xx) | Estimated
difference | P-value |
|-----------------------------------------------------------------------------------------------------------------------------------------------------------------------------------------------------------------------------------------------------------------------------------------------------------------|------------------------|-----------------------|-------------------------|---------|
| Demographic/Clinical                                                                                                                                                                                                                                                                                     |                        |                       |                         |         |
| Age, years                                                                                                                                                                                                                                                                                                      |                        |                       |                         |         |
| Male sex, no. (%)                                                                                                                                                                                                                                                                                               |                        |                       |                         |         |
| Height, m                                                                                                                                                                                                                                                                                                       |                        |                       |                         |         |
| Body mass, kg                                                                                                                                                                                                                                                                                                   |                        |                       |                         |         |
| Body mass index, kg/m                                                                                                                                                                                                                                                                               |                        |                       |                         |         |
| Injured knee (right), no. (%)                                                                                                                                                                                                                                                                                   |                        |                       |                         |         |
| Reconstruction graft type                                                                                                                                                                                                                                                                                       |                        |                       |                         |         |
| Time since surgery, month                                                                                                                                                                                                                                                                                       |                        |                       |                         |         |
| Knee joint laxity, mm                                                                                                                                                                                                                                                                                           |                        |                       |                         |         |
| Injury situation*, no. (%):                                                                                                                                                                                                                                                                              |                        |                       |                         |         |
| Traffic accident                                                                                                                                                                                                                                                                                                |                        |                       |                         |         |
| Sport injury                                                                                                                                                                                                                                                                                                    |                        |                       |                         |         |
| Other                                                                                                                                                                                                                                                                                                           |                        |                       |                         |         |
| Type of sport*, no. (%)                                                                                                                                                                                                                                                                                  |                        |                       |                         |         |
| Team ball sports                                                                                                                                                                                                                                                                                                |                        |                       |                         |         |
| Racket sports                                                                                                                                                                                                                                                                                                   |                        |                       |                         |         |
| Martial arts                                                                                                                                                                                                                                                                                                    |                        |                       |                         |         |
| Other                                                                                                                                                                                                                                                                                                           |                        |                       |                         |         |
| Return to sport*, no. (%)                                                                                                                                                                                                                                                                                |                        |                       |                         |         |
| No                                                                                                                                                                                                                                                                                                              |                        |                       |                         |         |
| Yes                                                                                                                                                                                                                                                                                                             |                        |                       |                         |         |
| Partly #                                                                                                                                                                                                                                                                                             |                        |                       |                         |         |
| Radiographic knee OA level (K-L score)§, no. (%)                                                                                                                                                                                                                                              |                        |                       |                         |         |
| 0                                                                                                                                                                                                                                                                                                               |                        |                       |                         |         |
| 1                                                                                                                                                                                                                                                                                                               |                        |                       |                         |         |
| 2                                                                                                                                                                                                                                                                                                               |                        |                       |                         |         |
| 3                                                                                                                                                                                                                                                                                                               |                        |                       |                         |         |
| 4                                                                                                                                                                                                                                                                                                               |                        |                       |                         |         |
| Activity level                                                                                                                                                                                                                                                                                           |                        |                       |                         |         |
| Pre-injury activity level (Tegner score)                                                                                                                                                                                                                                                                        |                        |                       |                         |         |
| Current activity level (Tegner score)                                                                                                                                                                                                                                                                           |                        |                       |                         |         |
| 
*Obtained during screening interview.
 
#Meaning “yes but not at the same pre-injury level”.
 
§Scores on the Kellgren–Lawrence scale range from 0 to 4, with a score of 2, 3, or 4 indicating definite osteoarthritis and higher scores indicating more severe disease.
 |                        |                       |                         |         |

